#### Faecal and saliva samples

Faecal samples will be collected at baseline (4–6 mo. of age), 12 and 18 mo. of age for analysis of microbiota composition. Analyses of the faecal microbiota composition will be done at the Paediatric Research Laboratory, Department of Clinical Sciences, Paediatrics, Umeå University, Umeå, Sweden. Any remaining faecal material will be stored in the Biobank of the Department of Clinical Sciences, Paediatrics, Umeå University, Sweden.

Saliva samples will be collected for genetic analyses. These will be done in collaboration with [name], The Center for Medical Genetics and Molecular Medicine, Haukeland University Hospital, Bergen, Norway. The analyses which include genome wide association studies (GWAS) as well as specific analysis of the bitter taste gene *TAS2R38* [61]. Homozygotic presence of the bitter-taste sensitive haplotype has been associated with lower intake of vegetables and higher intake of sweets in Finnish adults [62], but the effect on dietary intake during childhood is less clear [63]. In a separate sub-study we will explore genetic factors associated with weight development and the effects of complementary foods.

#### Developmental assessment

Child temperament, which may influence food acceptance will be assessed with the Swedish versions of the Baby Behaviour Questionnaire (BBQ) at baseline (4–6 mo. of age) and the Toddler Behaviour Questionnaire (TBQ) at 18 mo. of age [64]. To assess general cognitive and psychomotor milestones, the Ages and Stages Questionnaire (ASQ) [65] will be administered at baseline (4–6 mo. of age) and again at 12 and 18 mo. of age as a measure of general development.

A videotaped single object free play task [66, 67], as a measurement of cognitive development in relation to the nutritional intervention will be administered at 12 and 18 mo. of age at the time of the blood sample and anthropometric measurements. The test will be administered at the Paediatric Research Unit (Department of Clinical Sciences, Paediatrics, Umeå University, Umeå, Sweden). The videotapes will be assessed for cognitive development in association with associate professor [name], Karolinska Institute, Stockholm, Sweden. This methodology has been used when assessing cognitive effects of LCPUFAs in Danish infants [68].

#### Data on atopic disease and allergic manifestations

Family history of allergies, atopic diseases and asthma among parents and siblings will be collected at baseline. At 9, 12 and 18 mo. of age the participants will be asked for symptoms of allergy, asthma and atopic disease, and the research nurse will use a score sheet to assess eczema [69].

#### Symptoms registration

The participants will register days with symptoms of gastrointestinal disturbances (diarrhoea, constipation, vomiting), fever (≥38.0 °C), respiratory signs (cough, difficult breathing, coryza), sleep disturbances, skin symptoms, ear pain, teething, vaccinations, an estimate of the current appetite (decreased, normal, increased), if the child is being given medications and if the child has been seen by a doctor (because of illness) or if the child has been admitted to hospital. The forms will be filled out on paper and returned monthly to the researchers. At the monthly follow-up by a research nurse or dietician, these forms will be checked for completeness.

### Procedures

The baseline and 9, 12 and 18 mo. visits will take place at the Paediatric Research Unit at the Department of Clinical Sciences, Paediatrics, Umeå University Hospital.

At baseline, the researchers will establish that the participant fulfils all the inclusion criteria and none of the exclusion criteria, written informed consent will be collected if this has not been collected earlier and the parents will be given spoken and written information about the study and time to ask questions on the study procedures. The parents will also be given information on how to complete questionnaires and forms, whether on-line or on paper, how to upload photos and, if the participants are randomized to the ND group, how to access the on-line support forum, i.e. the closed Facebook group of the study. The participants will then be assessed according to the Figure including drawing blood samples and provided with a month’s supply of study products and recipes.

At ages 7 and 8 mo., the research nurse or dietician will have a telephone follow-up with the participants checking adherence, possible study related problems, supply and consumption of study products and symptoms registrations.

At age 9 mo. the participants will again come to the Paediatric Research Unit for measurements according to the Figure.

At ages 10 and 11 mo. the research nurse or dietician will have a telephone follow-up with the participants checking adherence, possible study related problems, supply and consumption of study products and symptoms registrations.

At 12 mo. of age, the participants will again come to the Paediatric Research Unit for providing samples according to the Figure. Further, the research nurse will do a home visit for anthropometric measurements, administration of the deuterium labelled water and the two videotaped tests, i.e. food acceptance test and the attention free play test.

At ages 13–17 mo., the research nurse or dietician will have a telephone follow-up with the participants checking adherence, possible study related problems, supply and consumption of study products and the symptoms registrations.

Finally, at 18 mo. of age, the participants will come for the final measurements of the study according to the Figure. The research nurse will again do a home visit for anthropometric measurements, administration of the deuterium labelled water and the two videotaped tests, i.e. food acceptance test and the attention free play test.

### Adverse events

An adverse event (AE) is any undesirable medical occurrence in a subject administered a study product, regardless of its cause. An adverse event can therefore be any unfavourable and unintended sign (including an abnormal laboratory finding), symptom, or disease temporally associated with the use of a study product, whether or not considered related to the study product. All adverse events, including observed or volunteered problems, complaints, or symptoms will be recorded on the Symptoms registration form. Each adverse event is to be evaluated for duration, intensity, and causal relationship with the study product or other factors. The participants will be instructed to report any AE that they experience to the researchers through the Symptoms registration form and by contacting the researchers. The research nurse will assess AE at each visit, i.e. 9, 12 and 18 mo. of age and at all monthly telephone follow-ups and report to the principal investigator (TL).

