### Study products

All participants will be supplied with study products free of charge. In the ND group, these will be specially prepared, protein-reduced, age-adjusted milk cereal drinks (MCDs), baby cereals and baby milk and commercially available baby foods in glass jars (BIG). The control group will be offered commercially available, age-adjusted MCDs, baby cereals, baby milk and BIG. Semper AB, Sundbyberg, Sweden, will provide all products.

The participants will be provided a month’s supply of study product at baseline and subsequently the families will come to the Paediatric Research Unit to collect more products as needed but not more than for one month at a time.

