#### The Nordic diet group

The Nordic diet group will experience three interventions (Fig. 1): i) a systematic introduction of taste portions, ii) milk cereal drinks (MCD), porridge and baby milk with reduced protein content, and iii) homemade and industry manufactured (BIG), protein-reduced main meals with a predominance of Nordic ingredients.When the parents have made the decision that their child should start with complementary foods, the ND group will be given instructions to systematically introduce four different fruits and berries (apple, raspberry, buckthorn/lingonberry, cranberry) and four vegetables (green peas, cauliflower, turnip, daikon), each one given at least 3 times daily for 3 consecutive days whether or not the child likes the flavour/consistency the first time or not. In total, there will be a maximum of 72 exposures during 24 days.When the parents start to complement the baby’s diet with MCD and/or porridge, the participants will be given protein-reduced products. The families will be instructed to use these products at their own discretion and they will have an offer to continue with these study products for as long as the child remains in the study.When the child is ready for a larger variation in meals, the ND group will be given recipes for main meals (lunch, dinner) and BIG with predominantly Nordic ingredients. The families can use these recipes and BIG as they see fit, but we will recommend that the families use the recipes for home-made food at least once daily.

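### Adverse-event causality is judged against the study product, not the whole assigned diet, so a reaction to home-made Nordic diet food has no category of its own

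*Protocol article*

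**What the plan says.** The Adverse events section uses the term study product in three ways.

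- **Whose events count:** an adverse event is "any undesirable medical occurrence in a subject administered a study product, regardless of its cause".
- **Timing:** signs, symptoms or disease qualify when "temporally associated with the use of a study product, whether or not considered related to the study product".
- **Causality:** "Each adverse event is to be evaluated for duration, intensity, and causal relationship with the study product or other factors".

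On recording, the section is broad: "All adverse events, including observed or volunteered problems, complaints, or symptoms will be recorded on the Symptoms registration form".

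The Study products section says what the term covers in the ND arm: "these will be specially prepared, protein-reduced, age-adjusted milk cereal drinks (MCDs), baby cereals and baby milk", plus commercial baby food in jars. Controls receive the ordinary commercial equivalents. All families get a first month's supply at baseline.

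The ND intervention is wider than this list. The Nordic diet group section names three components: systematic taste portions, protein-reduced drinks, porridge and baby milk, and main meals that are either home-made or from jars. Introduction of complementary feeding says that the taste portions are prepared at home from recipes. For main meals the article states that "we will recommend that the families use the recipes for home-made food at least once daily". The Procedures section lists recipes beside study products, not among them.

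**The concern.** The trial randomises children to a diet, of which the supplied products are one part. Causality is assessed against that part alone. The omitted part, the ND taste-portion scheme and recipes, is given to one arm only.

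A statement about events related to the intervention would therefore leave out the home-made component. The classification also reaches the Withdrawal section, where adverse events are one of the listed reasons for leaving the study.

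The start of feeding adds a second, narrower gap. Infants who already take complementary food are excluded at recruitment, so the taste phase is the child's first contact with such food. If no product has yet been used, the wording does not clearly make an event in that phase an adverse event at all.

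**Working it through.** No figure in the protocol bears on this point and no formula applies. The check sets the sections side by side.

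1. **Is home-made food a study product?** No. Study products lists only supplied items, and Procedures names recipes as a separate item.

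2. **Is home-made food part of what was randomised?** Yes. It makes up the first ND component and is one of the two forms of the third, so two of the three components are wholly or partly home-made. Controls receive no recipes (The regular diet group).

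3. **Where does the causality rule put a reaction to an ND puree or recipe meal?** The rule names two destinations, the study product or other factors. By step 1 the food is not a study product, so the event goes to other factors. By step 2 it was nevertheless caused by the assigned intervention. This applies throughout follow-up.

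4. **Is such an event counted as an adverse event?** This depends on when it occurs.
   - *After first product use:* yes. The definition applies regardless of cause and does not require relatedness, so the event counts in the child's randomised arm.
   - *Before first product use:* read strictly, no, because the child has not yet been given a study product.

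5. **Can there be an interval before first product use?** Yes, but its length is unknown. The taste scheme runs 8 foods × 3 days = 24 days. Drinks and porridge have their own start, chosen by the parents, and are used at the family's discretion. Products are in the home from baseline, and no product-free interval is prescribed.

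6. **Is the underlying information lost?** Largely not. The symptom form registers gastrointestinal, skin, respiratory and other symptoms, medication, doctor visits and admissions without reference to product. Allergy, asthma and atopic symptoms are asked about at 9, 12 and 18 months, and the nurse scores eczema. However, the listed form items do not include the food suspected.

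**The case against.** The strongest reply is that the study product serves to identify the child, not the cause. Events count whatever their cause, every family in both arms has products from baseline, and symptoms and allergy are collected independently of product use. The same definition applies in both arms, and control families also start small taste meals on standard advice. The category of other factors is open and does not stop an assessor from naming a recipe food. The article plans no analysis of related events, and detailed causality coding may be set out in a fuller protocol.

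Most of this stands, and it rules out a stronger reading. A reader might infer that reactions to home-made food are left out of the adverse-event count, or that ND events are understated relative to control. The documents support neither. After first product use such events are counted in their arm, between-arm comparisons of symptoms remain possible, and the early gap meets both arms under the same wording. Differential undercounting is not shown.

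The attribution rule is not rescued. The article does not leave causality to another document: it states the rule and names one object for it. An open remainder category mixes a reaction to the assigned diet with intercurrent illness unless someone records the food, and nothing in the article requires that.

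**Conclusion.** The point holds as a defect of attribution, with a narrow defect of counting before first product use. Relatedness is assessed against only part of the randomised intervention, and the part left out is specific to the ND arm. A future statement that no events were related would cover the supplied products but not the diet.

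The size cannot be given as a number. The document has no event rates and does not say how long children eat taste portions before any product. The primary outcome, fat mass, is unaffected.

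The conclusion rests on two assumptions: that study product carries the meaning given in the Study products section wherever it is used, and that assessors apply the causality rule as written. The change is worth making because safety attribution in infants should match what was randomised.

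**What to change.** - **Definition.** Count as an adverse event any undesirable medical occurrence in a randomised child from randomisation to the 18-month visit, irrespective of product use.
- **Causality.** Assess relatedness to the whole assigned diet by the same rule in both arms. In the ND arm this means products, taste portions and recipe meals; in the control arm, products and foods given under the standard feeding advice. Relatedness to a supplied product can be kept as a subcategory.
- **From now on.** Where a reaction to food is suspected, note the food at the monthly call or visit.
- **Forms already returned.** Re-classify only where the form, or the notes from the monthly calls, holds enough information. Do this preferably without knowledge of arm, and report how many events could not be attributed. A named recipe food may itself reveal the arm, which should be acknowledged.

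The cost is a change of wording, at most one extra note per suspected reaction, and somewhat more classification work. Retrospective attribution will be incomplete because the form's listed items do not ask for the suspected food. Data collection was due to run until February 2019, so by the article's own timetable the change could be made before analysis.

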### Withdrawal

The participants may withdraw from the study at any time by i) withdrawing consent, ii) through non-compliance (repeated failure to comply with study procedures) or if iii) the participant experiences adverse events requiring the participant to withdraw on advice of the research physician or by his/her own accord. If possible the researchers will explore the specific reasons why consent was withdrawn, type of non-compliance and which specific AEs that caused withdrawal. All reasons for withdrawal will be recorded. Participants who withdraw will not be replaced.

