#### Exclusion criteria

Children with chronic illnesses that will affect feeding or growth, including food allergies or intolerance to study productsIntake of any complementary food at recruitmentUse of supplements or medications that will affect the study outcomesIron deficiency (Hb < 105 g/L, serum (S-) ferritin < 12 μg/L) or any other biochemical abnormality discovered at the baseline examination that needs medical attention after decision by the study physician.Repeated non-adherence to key study procedures including anthropometric measurements, allergy, eczema and symptoms registrations.

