### Power calculation and statistical analyses

The primary outcome of the study is body composition, i.e. fat mass measured by TBW. The body fat mass is on average 2.9 ± 0.6 kg at 12 mo. of age. In order to detect a difference in body fat of 0.24 kg between the intervention (ND) and control groups at 12 mo. of age (α = 0.05, power = 80%) with an attrition of 20%, we will need 125 participants per group.

Comparisons of differences in main outcomes between the ND and control groups will be the focus of the statistical analyses. The primary outcomes will be analysed according to the intention-to-treat principle when comparing the two study groups, but per protocol analyses will also be done. Both parametric and non-parametric tests will be used depending on the distribution of data. Possible effect modifiers and confounders will be included in the analyses as needed to explain group differences. Data on dietary intake will be converted to energy and nutrients through nutrient calculation software (Dietist NET, Kost och Näringsdata AB, Bromma, Sweden).

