## Discussion

The early diet has long-lasting effects on human health. Apart from breastfeeding, little is known about which infant diets would confer long-term health benefits. ND has several potential advantages in this respect, and studies in adults have shown favourable effects on metabolic- and cardiovascular disease markers and mortality similar to those gained through the Mediterranean diet. The present study, using ND as the basis for complementary foods but also reducing the total protein intake, improving fatty acid composition and expanding the introduction of fruits and vegetables into the diet of young children will add vital information in the quest to prevent obesity, dyslipidaemia, insulin resistance, type 2 diabetes, hypertension and cardiovascular disease. If the objectives of the study are reached it will thus serve to improve dietary recommendations to infants in Sweden and worldwide. Strengths of the study include individual randomization of the participants, use of well-validated methods of data collection and analysis and close follow-up and support to the participants through dedicated research staff. Possible limitations include difficulties of the families accepting and adhering to the ND, which may lead to higher drop-out rate in the intervention group. The focus on ND may also skew recruitment away from non-Nordic participants. However, this will most likely not affect the outcomes.

Through early intervention, i.e. already when complementary foods are introduced into the diet of the infant, we believe that we can initiate healthy food preferences from the earliest date, thus optimizing the long-term public health benefits. By adopting the concept of ND we will also add gastronomical aspects to the development of optimal complementary foods as well as support regional food production and contribute to a sustainable environment.

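### An adverse event that requires stopping is handled as withdrawal from the study, with no stated option to stop the study foods and still be measured, although the primary analysis is intention-to-treat

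*Protocol article*

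**What the plan says.** The Withdrawal section of the protocol article describes one kind of exit, from the study: "The participants may withdraw from the study at any time by i) withdrawing consent, ii) through non-compliance (repeated failure to comply with study procedures"), or "iii) the participant experiences adverse events requiring the participant to withdraw on advice of the research physician or by his/her own accord". On what follows, beyond exploring the specific reasons where possible, it states: "All reasons for withdrawal will be recorded. Participants who withdraw will not be replaced". It mentions no measurement after that.

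Other sections bear on the point:

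- **Power calculation and statistical analyses:** "The primary outcomes will be analysed according to the intention-to-treat principle when comparing the two study groups". A per-protocol analysis is added.
- **Discussion:** among the possible limitations are "difficulties of the families accepting and adhering to the ND, which may lead to higher drop-out rate in the intervention group".
- **Body composition:** fat mass is determined at 12 and 18 months. There is no baseline determination.
- **Dietary intake, eating behaviour and food acceptance:** the videotaped test meal is also at 12 and 18 months.
- **Data on atopic disease and allergic manifestations:** "At 9, 12 and 18 mo. of age the participants will be asked for symptoms of allergy, asthma and atopic disease", and eczema is scored at the same visits.
- **The Nordic diet group:** for the protein-reduced cereal and milk products, "The families will be instructed to use these products at their own discretion". Recipes and jarred foods are likewise left to the family's choice, with daily home-made food only recommended.

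**The concern.** Stopping an intervention and leaving a trial are different events. For an adverse event judged to require stopping, the Withdrawal section gives only the second. The children concerned may be those who reacted to the study foods, so their loss may depend on allocation and on the outcome. Take an infant withdrawn at 7 months after a reaction to a study food. That child has none of the 9-, 12- and 18-month allergy and eczema assessments, and allergy is a listed outcome in Table 1.

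For fat mass the loss is complete when withdrawal comes before 12 months, because no earlier determination exists. Intention-to-treat then places the child in the allocated arm without an observed outcome, and the estimate depends on assumptions about the missing values. The authors themselves raise the possibility of unequal drop-out linked to the diet, but the article states no step to keep measuring these children.

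**Working it through.** **1. The plan's own sample size.** Inputs from the power section: SD 0.6 kg, difference 0.24 kg, α = 0.05 (taken as two-sided), power 80%, attrition 20%.

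- n per arm = 2 × (1.960 + 0.842)² × (0.6/0.24)² = 2 × 7.85 × 6.25 ≈ 98.1, so 99 evaluable.
- 99/0.8 = 123.75, so 124. The plan states 125, which equals 100/0.8. With 100 per arm, power is 80.4% (t distribution) or 80.7% (normal approximation).

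The figure reproduces and is not in dispute.

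**2. Power or bias?** Uneven loss alone costs little power. With 88 ND and 113 control children measured (an assumed split), power is 80.3%. With 75 and 112 it is 76.5%. The issue is mainly bias.

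**3. Size of a possible bias.** Let q be the share of the ND arm lost for diet-related reasons, C the completer mean and S the mean among those lost. The full-arm mean is (1 − q)C + qS, so the completer mean is off by C − [(1 − q)C + qS] = q × (C − S). Write D for the absolute value of C − S. Control losses are taken as unrelated to outcome. The documents give neither q nor D, so both are assumptions.

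| q | D = 0.1 kg | D = 0.3 kg | D = 0.5 kg |
|---|---|---|---|
| 10% | 0.010 kg (4% of 0.24) | 0.030 kg (12.5%) | 0.050 kg (21%) |
| 25% | 0.025 kg (10%) | 0.075 kg (31%) | 0.125 kg (52%) |

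The upper row of q is generous to the concern. Suppose attrition were 25% in ND and 15% in control, averaging the planned 20%, and ND shared the same 15% random loss. Diet-related stoppers would then be 10/85 = 11.8% of the rest. At D = 0.3 kg the shift would be 0.118 × 0.3 ≈ 0.035 kg (15% of the target), not 0.075 kg.

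These values of q cover all diet-related loss. Withdrawal for adverse events is only part of that, and the documents do not say how large a part.

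**4. Who is affected.**

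| Situation | What the article provides | Later measurements |
|---|---|---|
| Child refuses ND foods, or family uses few or none | Use is discretionary; non-compliance concerns study procedures | Continue |
| Adverse event not judged to require withdrawal | Recorded and assessed at visits and monthly calls | Continue |
| Adverse event judged to require withdrawal | Withdrawal from the study | None stated |
| Family withdraws consent | Withdrawal from the study | None, properly so |

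Only the third row is a defect of the rule.

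**The case against.** A reader might infer that leaving the study is the only way to stop the diet, so that children who refuse Nordic foods also lose their measurements. The documents do not support this. The Nordic diet group section leaves use of the foods to the family and tells parents to keep offering tastes the child dislikes. Non-compliance is defined by study procedures, and the Exclusion criteria illustrate it with "Repeated non-adherence to key study procedures including anthropometric measurements, allergy, eczema and symptoms registrations", not with eating the diet. A child who rejects the foods can stay and be measured. A family that leaves anyway is withdrawing consent, and no rewording would recover it.

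It can also be said that the adverse-event route covers only events that require withdrawal or a family's own choice to leave. In addition, each event is evaluated for duration, intensity and causality, and the events that led to withdrawal are to be explored where possible. That stands: a reaction is documented. But a record of the event does not replace the later allergy, fat-mass or test-meal assessments.

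The strongest objection is that this is a condensed article, and that follow-up after stopping may be set out in the full protocol. It may be. Still, the article does more than stay silent: it states that such an adverse event leads out of the study. If the full protocol provides otherwise, the two should agree. Intention-to-treat concerns analysis by allocation and is not contradicted by attrition as such. The difficulty is avoidable loss of outcomes in children whom it is meant to include.

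Finally, the Discussion says only that drop-out may be higher in the ND arm. It gives no rate and does not say that this will happen.

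**Conclusion.** The point holds in a limited form. Adverse events that require stopping are treated as withdrawal from the study, with no stated way to stop the study foods and keep the planned measurements. This fits poorly with intention-to-treat and with the authors' own caution about drop-out in the ND arm. Children who merely eat little or none of the ND foods are outside it.

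Under the assumed ranges (10% to 25% diet-related ND loss, 0.1 to 0.5 kg difference, control losses unrelated to outcome), the shift in mean fat mass is 0.01 to 0.125 kg, or 4% to 52% of the 0.24 kg target. This shows scale and is not an estimate. A reader might infer that the bias favours the Nordic diet, but nothing in the documents fixes its direction for fat mass. For allergic manifestations, the later assessments would be missing for any child withdrawn because of a reaction. How many such children there are is unknown. The point is a cheap improvement, not a flaw that invalidates the design.

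**What to change.** Reword the Withdrawal section to distinguish two events:

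1. **Stopping study foods**, for any reason including an adverse event. The child stays in the study and is still invited to the scheduled 9-, 12- and 18-month assessments (anthropometry, deuterium dose, test meal, allergy and eczema assessment, each at its planned age). Parents are free to decline any procedure.
2. **Withdrawing consent to further data collection**, which alone ends follow-up.

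State that children in the first group are analysed in their allocated arm under intention-to-treat. When and why a child stops a food remains with the study physician, and this change proposes no clinical rule. The Exclusion criteria, The Nordic diet group, Withdrawal and the statistical section should be reconciled. In particular, it should be clear whether the listed exclusions for intolerance to study products and for repeated non-adherence to procedures apply after randomisation.

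**Cost:** the visits are already scheduled for every child, so the main cost is protocol and consent wording. Trial status reports that recruitment ended in February 2018 with 250 children and that data collection runs to February 2019. The change would therefore alter terms for families already enrolled and could help only with visits still to come. Including children who stopped the foods may also dilute the observed diet effect.
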